## Abstract

**Background:**

Physiotherapy is a proven effective treatment strategy after total knee and hip arthroplasty (TKA/THA), however there is considerable practice variation regarding its timing, content and duration. This study aims to compare the (cost-) effectiveness of a standardized, treat-to-target postoperative physiotherapy strategy with usual postoperative care.

**Methods:**

Using a cluster randomized study design, consecutive patients scheduled for a primary TKA/THA in 18 hospitals in the Netherlands will be assigned to the treat-to-target physio therapy strategy or usual postoperative care. With the treat-to-target strategy a standardized, individually tailored, exercise program is aimed at the attainment of specific functional milestones. Assessments are done at baseline, 6 weeks and 3, 6, 9 and 12 months follow up. The primary outcome will be the Knee injury / Hip disability and Osteoarthritis Outcome Score - Physical Function Short Form (KOOS-PS / HOOS-PS) at 3 months follow up. Secondary outcomes are the numeric rating scale for pain, the Oxford Knee and Hip Scores, performance-based test and the EuroQol 5D-5L for quality of life. Healthcare use, productivity and satisfaction with postoperative care are measured by means of questionnaires. In total, 624 patients will be needed of which 312 TKA and 312 THA patients.

**Discussion:**

The study will provide evidence concerning the (cost-) effectiveness of the treat-to-target postoperative physiotherapy treatment compared to usual postoperative care. The results of this study will address an important evidence gap and will have a significant impact in daily practice of the physio therapist.

**Trial registration:**

Registered in the Dutch Trial Registry on April 15, 2018. Registration number: NTR7129.

## Background

In patients undergoing total knee or hip arthroplasty (TKA/THA) for osteoarthritis (OA) postoperative physiotherapy (PPT) is a recommended treatment [1–4]. Several studies have demonstrated its effectiveness in improving function, range of motion and quality of life [5–8]. Moreover, PPT also seems to play an important role in achieving functional independence such as return to work [9, 10].

Despite the current evidence, there is no consensus on the optimal composition of the treatment, timing (when to start and stop), and dosage (frequency). This has led to considerable practice variation, as demonstrated by a number of studies [11–13]. For instance, a Dutch multicenter study on 522 TKA and THA patients found variation in the use of active and passive treatment modalities, and large individual differences in duration of treatment [14]. Potential sources of variation are constituted by different postoperative treatment protocols used by orthopedic surgeons and hospital physio therapists (PTs) [15], as well as variation among primary care PTs delivering the intervention. About 1.66 and 1.26 per 1000 people receive TKA or THA respectively in western countries each year [16]. From the health care and societal perspective, it is highly relevant that the most optimal PPT treatment strategy is used. Therefore, more knowledge on optimized PPT strategies is necessary [16, 17].

It is conceivable that PPT may be optimized by using a standardized treatment, that is tailored to the patient’s individual situation. Previous research has shown that targeting treatment using specific milestones, also called treat-to-target strategy, was found to assist physicians in disease management, by simplifying and facilitating disease management decisions [18]. It is proven effective in improving clinical outcomes in various chronic conditions such as, cardiovascular disease and rheumatoid arthritis [12, 19, 20]. However, milestones are currently not routinely used in PPT after TKA or THA to direct treatment. Another way via which care can be optimized is by use of a transmural care pathway, which includes a short stay (1–2 days) and acute (secondary care) and post-acute care (primary care). In TKA and THA these transmural pathways are known to result in less postoperative complications, shorter length of hospital stay and lower costs during hospital stay when compared to standard care (3–4 nights inpatient) [21–23]. Hence, a transmural pathway for PPT after TKA and THA linking all organizational aspects related to the continuum of TKA/THA care might also improve PPT. As such, we propose an individualized PPT intervention that is relatively standardized, yet the precise content, frequency and duration of treatment are determined by the acquisition of individualized, functional milestones. This research topic was prioritized on the research agenda of the Dutch Orthopaedic Association (NOV). Within this project, the NOV and the Royal Dutch Society for Physio therapy (KNGF) collaborate.

## Trial objectives

The aim of the present study is to evaluate the (cost-) effectiveness of a standardized, treat-to-target PPT strategy in TKA and THA patients compared to usual PPT. We hypothesize that with the standardized treat-to-target strategy better functional outcome can be achieved compared to usual care with lower costs (superiority study). The results of this study will be used to develop and implement a nationwide treatment strategy for PT after TKA/THA, and will be integrated in national guidelines of PTs and orthopedic surgeons.

Primary objective
To assess whether the functional outcome of a standardized, personalized treat-to-target PT strategy after TKA and THA is superior to usual care PPT after 3 months follow-up.To assess whether a standardized, personalized treat-to-target PPT strategy is more cost-effective compared to usual care PPT after 12 months follow-up.

Secondary objective
To assess whether the functional outcome of a standardized, personalized treat-to-target PPT strategy after TKA and THA is superior to usual care PPT during the follow-up of 12 months.To assess the difference in function, performance-based tests, pain and quality of life, as well as anchor questions, and satisfaction question; between both groups over time (6 weeks, 3,6,9 and 12 months) during the first year.

## Methods/design

### Study design and setting

We will use a multicenter, cluster randomized design. The 18 active including centers are; Alrijne hospital (Leiderdorp), Bergman Clinics (Rijswijk), Canisius Wilhelmina hospital (Nijmegen), Diakonessenhuis (Utrecht), Elisabeth-Tweesteden hospital (Tilburg), Erasmus MC University Medical Center (Rotterdam), HAGA hospital (Den Haag), hospital Gelderse Vallei (Ede), Leiden University MC (Leiden), Máxima MC (Eindhoven), MC Leeuwarden, Northwest Clinics (Alkmaar) OLVG (Amsterdam), Spaarne hospital (Hoofddorp), Tergooi hospital (Hilversum), University MC Groningen, University MC Maastricht and Zuyderland MC (Sittard). Lange Land hospital (Zoetermeer) and Reinier de Graaf Gasthuis (Delft) are participating in the study however they are not including patients. Reinier de Graaf is involved in developing the PPT protocol and a part of the patients of HAGA hospital will have surgery in Lange Land hospital.

In the intervention group, PT is delivered by selected primary care practices by specially trained PTs. The training is a physical training and will be given by the same project members. In the control group the choice to use PT and the primary care practice is left to the discretion of the orthopaedic surgeon and the patient. In the Netherlands, after TKA or THA, a referral from the orthopaedic surgeon is needed for the healthcare insurance. This referral is standardly given by discharge from the hospital.

The planned duration of the study is three years.

The study protocol was reviewed and approved by the Erasmus MC Medical Ethics Committee (registration code NL61763.078.17) and was registered in the Dutch Trial Registry (registration number NTR7129). In all participating hospitals, the local responsible authorities approved the conduct of the study.

### Study population

#### Inclusion and exclusion criteria

##### Inclusion

Patients eligible for this trial are; a. patients with clinical and radiological knee or hip OA who are scheduled for a primary TKA or THA, b. willing to comply with the study protocol and c. providing written informed consent.

##### Exclusion

Patients with a TKA or THA for a diagnosis other than OA; b. uncontrolled cardiovascular disease or hypertension; c. history of neuromuscular disorder that affects lower extremity function, d. terminal illness; e. planned replacement of another joint during study follow-up; f. not able to attend follow-up measurements; g. not able to attend the PPT in primary setting; h. serious psychiatric disorders; i. insufficient command of the Dutch language, spoken and/or written.

#### Recruitment

Patients who are scheduled for a primary TKA or THA in one of the participating hospitals and meet the eligibility criteria will be informed about the study by means of oral and written information. After written consent, baseline measurements are carried out. Recruitment is done by an orthopedic surgeon or researcher on his/her behalf.

#### Blinding

The study is an open-label trial.

### Intervention

#### Development treat-to-target intervention

The treat-to-target PPT is presented in the form of a transmural care pathway and was developed in four different phases knowingly, 1) an inventory phase, 2) development of the first draft, 3) development second draft, 4) finalizing treat-to-target PPT (Fig. 1). In the first phase, a literature study on the efficacy of PPT was done, in which guidelines regarding THA and TKA were taken into account. Also, an assessment of the existing perioperative treatment protocols in the Netherlands was conducted. Based on a selection of best practice (integrality and evidence based), one protocol was selected as the fundament for our treat-to-target intervention. In the second phase this protocol was adapted and supplemented using literature and guidelines. Hereafter the first concept of the protocol was discussed in an expert meeting of one primary and one secondary PT, a patient and orthopedic surgeons. In the third phase, the concept protocol was adjusted and details regarding the implementation in daily practice were added by 2 PTs who have extensive experience in the field of developing treatment protocols. The second concept of the protocol was again presented to the PTs, the patient and orthopedic surgeons who attended the first expert meeting for feedback. In the fourth and last phase, the protocol was adjusted based on the feedback of the expert panel resulting in final our treat-to-target intervention. This intervention consists of a preoperative assessment by the primary PT, secondary PPT and a comprehensive and personal transferal from the hospital PT including a Modified Iowa Levels of Assistance Scale (MILAS) score as a starting point of the secondary PPT.

**Fig. 1 Fig1:**
[figure not shown]
Development PATIO treat to target intervention care pathway

#### Intervention arm: treat-to-target intervention

First the necessity of PPT will be screened by a standardized assessment of the patient’s health status, personal-, external factors and achievement of functional milestones. This assessment will be performed by the primary care PT in the first appointment after surgery (within 3 days after discharge from the hospital). Those needing PPT in primary care receive a standardized, personalized, time contingent program, focused on evidence-based components such as muscle strengthening and functional exercises. Exercises, selected by the PT, are available via an app or printed by the PT via Physitrack, an online available exercise program. The progress of functioning of the patient will be regularly evaluated regarding achievement of functional milestones. After reaching the milestones, PPT is ended and patients will receive a tailored advice with home-based exercises in combination with referral to exercise activities in the community.

#### Control arm: usual care

The use of PT and the choice of the physical therapist, is left to the discretion of the treating physician and the patient.

### Assessments

Patients will be asked to fill in questionnaires at baseline, and at 6 weeks, 3- (primary end-point), 6-, 9 and 12-months follow-up. Performance-based tests will be performed at baseline, 6- and 12 months (see Table 1 for an overview). In each participating hospitals an assessor will be trained by the coordinating researcher to perform these Performance-based tests.

**Table 1 Tab1:** Overview of measurement PATIO study

Timepoint	Allocation	Enrolment	Post-allocation	Close-out
	Randomization	Baseline, at inclusion	6 weeks,3, 6, 9 –months follow-up	12-months follow-up
Enrolment				
Eligibility screen		X		
Informed consent		X		
Allocation	X			
Interventions				
*Intervention group: Treat to target*			X	X
*Control group:* *Usual care*			X	X
ASSESSMENTS:				
*Demographic;* age, gender, side affected, BMI, education level, comorbidity		X		
*HOOS-PS / KOOS - PS*		X	X	X
*OHS / OKS*		X	X	X
*NRS*		X	X	X
*AAQ*		X	X (only at 3 months)	X
*EQ 5-D5L*		X	X	X
*Satisfaction question*			X	X
Cost-effectiveness			X	X
*Performance-based tests*		X	X (only at 3 months)	X
*(Serious) Adverse events*			X	X

#### Patient characteristics

At baseline the following patient characteristics will be obtained: age, sex, side affected, height, weight, education level, ethnical background, living situation (living alone, living with partner, living with partner and child (ren) and living with children), duration of complaints, previous surgery and existing comorbidities.

### Primary outcomes

#### Physical functioning

Physical functioning, assessed by the 5-item short version of the validated Dutch translation of the Hip disability and Osteoarthritis Outcome Score (HOOS) [24, 25] or the 7-item short version of the Dutch translation of the knee injury and Osteoarthritis Outcome Score (KOOS) questionnaire [26, 27]. Function scores will be determined on a scale from 0 (severe impairments in function) to 100 (no impairments in function).

### Direct and indirect costs

Medical consumption (visits to health care providers and usage of prescribed or over the counter medication), absence from work or decreased productivity at work, and patient costs to be able to do cost-effectiveness analysis will be assessed with a questionnaire at 3,6,9 and 12 months postoperative. Our questionnaire is based on the questionnaire for Costs associated with Psychiatric Illness (TiC-P) from the institute of medical technology assessment [28]. We have left out the irrelevant questions about psychiatric consultations. We added questions about PT consultation (frequency) and specified medication in use of pain medication.

### Secondary outcomes

#### Pain and functioning

##### Performance-based test

Performance-based test as recommended by Osteoarthritis Research Society International (OARSI) [29] namely, 30 s “chair-stand test”, “40m walk test” and “stair negotiation” test, will be evaluated by the assessor. Assessors in all participating hospitals are trained in using a Dutch translated OARSI protocol. These tests will be performed at baseline, 3 months and 12 months.

### Self-reported pain and function

#### Numeric Rating Scale

Hip and knee pain severity in rest and during activities in the past week will be assessed by the Numeric Rating Scale (NRS) [30]. Scores range between 0 (no pain) and 10 (worst pain imaginable).

#### Oxford Hip score / Oxford Knee Score

Pain intensity and functional limitations in daily activities will be assessed by the Oxford Hip score (OHS) [31] and the Oxford Knee Score (OKS) [32]. Both consist of 12 questions; each question will be scored from 0 to 4 with 4 being the best outcome. Overall scores running from 0 to 48 with 48 being the best functional outcome.

#### The Animated Activity Questionnaire (AAQ)

Basic daily activity limitations will be assessed with the Animated Activity Questionnaire (AAQ) [33] in which patients see video animations of 17 different basic daily life activities. These activities closely mimic real-life situations. For each activity, three to five different levels of difficulty in performing the activity are shown as video animations at the same time. The patient is asked to choose the video that best matches his or her own performance. Function scores will be determined on a scale from 0 (severe impairments in function) to 100 (no impairments in function). This video animated questionnaire will be assessed during the physical assessment appointment at baseline, 3 months and 12 months.

### Quality of life

#### EuroQol-5D-5L

Health-related quality of life will be assessed by the EuroQol-5D-5L (EQ-5D-5L) [34]. This questionnaire consists of five domains (mobility, self-care, daily activities, pain/discomfort, and anxiety/depression) in which the patient can self-rate their severity of problems on a 5-point scale ranging from no problems to extreme problems or unable to perform the task.

### Postoperative physical therapy (PPT)

Based on experiences in previous studies among physical therapists and patients [14], we will retrospectively evaluate, in the intervention group, the care of the PPT and the compliance of the patients by asking the physical therapists and patients to fill out predefined report forms [14]. The set of questions comprised the survey regarding PPT. In a random sample of 5% we will evaluate the status of the patient of the participating physical therapist what the given PPT care was (content, duration, frequency), and whether this agrees with the case report forms as described above.

In the control group we will also retrospectively evaluate the content, duration and frequency of the PPT with the same report forms.

### Process evaluation

#### Anchor and satisfaction questions

Two anchor questions (“How is your daily functioning changed since your surgery?”/ “How are your pain complaints changed since your surgery?”, a patient satisfaction question on their surgery (“How satisfied are you (in general) about the results of your surgery?”), and a question regarding the given PPT (“How satisfied are you (in general) about the results of your PT treatment?”) will be evaluated at all postoperative time points.

#### (Serious) adverse events & dropout rates

Any (S)AE will be communicated by the local researcher to the central researcher as soon as they become aware of it. The central researchers will report a SAE by the Centrale Commissie Mensgebonden Onderzoek (CCMO) via Toetsingonline within 7 (death or life threatening situations) or 15 (remaining SAE’s) days. All drop-outs and protocol violations will be recorded.

An overview of the assessments can be found in Table 1.

## Sample size and power calculation

Our primary research hypothesis is that the improvement in physical function in our “treat-to-target” intervention will be superior to the improvement in the usual care group at 3 months, measured by the HOOS-PS/KOOS-PS score.

The power calculation is based on the proof of superiority, and calculated for patients undergoing TKA and THA separately. The reported standard deviation (SD) of the KOOS-PS and HOOS-PS 3 months after physiotherapy in TKA and THA patients was 15.6 and 11.8, respectively [35–41]. For the intra cluster correlation coefficient we used an interclass correlation coefficient (ICC) of 0.06, which is generally reported in literature for hospital processes. To detect superiority of the treat-to-target PPT intervention to usual PPT we assessed the required sample size based on the following assumptions, a minimally clinical important difference (MCID) of 10 points, and a SD of 15.6. Since a MCID of the KOOS-PS and HOOS-PS after postoperative physiotherapy in TKA/THA patients is not yet available, a MCID was chosen based on expert opinion, namely 10 points on the KOOS-PS and HOOS-PS [42, 43].

### Primary outcome

We propose a cluster RCT (randomization on hospital level) with an intracluster correlation coefficient of 0.06 and in total 18 participating hospitals. Sample sizes of 90 in group one and 90 in group two, which were obtained by sampling 9 clusters with an average of 10 subjects each in group one (180 patients) and 9 clusters with an average of 10 subjects each in group two (180 patients), achieve 90% power to detect a difference between the group means of at least 10. The coefficient of variation of cluster sizes is 0,500. A two-sided t-test was used with a significance level of 0,05. This test used degrees of freedom based on the number of subjects. To account for a 25% of drop out 240 TKA and 240 THA patients will be needed.

### Secondary outcomes

We also assessed the needed numbers to detect superiority of the treat-to-target PPT intervention to usual PPT for the outcome improvement of pain severity as assessed by the NRS. Based on a MCID of 1 point on the NRS, and a SD of 2 the needed numbers were assessed. Sample sizes of 117 in group one and 117 in group two, which were obtained by sampling 9 clusters with an average of 13 subjects each in group one (234 patients) and 9 clusters with an average of 13 subjects each in group two (234 patients), achieve 91% power to detect a difference between the group means of at least 1. The SD of subjects is 1.7. The intracluster correlation coefficient is 0.06. The coefficient of variation of cluster sizes is 0.500. A two-sided t-test was used with a significance level of 0.05. This test used degrees of freedom based on the number of subjects. To account for a 25% of dropout,624 patients will be needed of which 312 TKA and 312 THA patients.

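### The NRS pain calculation that sets the trial size at 624 names an SD of 2 but was run with 1.7; at SD 2 the power is about 79–80%, not 91%

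*Protocol article*

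**What the plan says.** The calculation is in the protocol article under Sample size and power calculation, subsection Secondary outcomes. It is introduced with a target difference and an SD: "Based on a MCID of 1 point on the NRS, and a SD of 2 the needed numbers were assessed". It then gives the result, "Sample sizes of 117 in group one and 117 in group two", made up of 9 clusters per arm with a mean of 13 patients, which "achieve 91% power to detect a difference between the group means of at least 1". The remaining inputs follow: "The SD of subjects is 1.7", "The intracluster correlation coefficient is 0.06", "The coefficient of variation of cluster sizes is 0.500" and "A two-sided t-test was used with a significance level of 0.05", with degrees of freedom based on subjects. Allowing for 25% dropout, the paragraph arrives at 312 TKA and 312 THA patients, 624 in all.

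The preceding subsection, on the primary outcome, needs 240 patients per joint after dropout, which is 480. The Abstract gives only the 624.

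**The concern.** One calculation cannot have two SDs for the same outcome. The paragraph presents 2 as the basis for the required numbers and then lists 1.7 among the inputs behind the 91%. Nothing in the article connects the two values or gives a source for either.

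Two things depend on this. First, the 144 patients added to the primary-outcome requirement (624 − 480) are justified by this paragraph alone, so its stated premise should support its stated result. Second, readers of a null pain result will take the comparison to have had 91% power for a 1-point difference. If the SD is 2, the chance of missing such a difference is about one in five rather than one in eleven.

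**Working it through.** **Inputs**, all from the paragraph on secondary outcomes: difference 1 point; 9 clusters per arm, mean size m = 13, so n = 117 per arm per joint; ICC 0.06; CV of cluster size 0.5; two-sided α = 0.05; subject-based df = 2 × 117 − 2 = 232; SD either 1.7 or 2.

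**Design effect.** The article does not say how unequal cluster sizes were handled, so two common forms were used.

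- Relative-efficiency form: λ = m·ICC / (m·ICC + 1 − ICC) = 0.78 / 1.72 = 0.4535. DE = [1 + (m − 1)·ICC] / [1 − CV²·λ(1 − λ)] = 1.72 / 0.938 = 1.834.
- Simpler form: DE = 1 + [(1 + CV²)·m − 1]·ICC = 1 + (16.25 − 1) × 0.06 = 1.915.

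**Power.** SE = SD × √(2·DE / 117) and noncentrality = 1 / SE, with power from the noncentral t distribution on 232 df.

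| SD | DE | SE | Noncentrality | Power |
|---|---|---|---|---|
| 1.7 | 1.834 | 0.301 | 3.32 | 91.1% |
| 1.7 | 1.915 | 0.308 | 3.25 | 89.9% |
| 2 | 1.834 | 0.354 | 2.82 | 80.3% |
| 2 | 1.915 | 0.362 | 2.76 | 78.6% |

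The article's 91% is therefore reproduced with SD 1.7, exactly so under the relative-efficiency form. It is not reproduced with SD 2.

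**Dropout.** 2 × 117 = 234 per joint; 234 / 0.75 = 312; two joints give 624. This step is correct.

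**Could something else explain the two values?**

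- Total versus within-cluster SD: a total SD of 2 with ICC 0.06 implies a within-cluster SD of 2 × √0.94 = 1.94, not 1.7.
- Cluster-size variation: ignoring it (DE 1.72) still gives only 82.7% at SD 2.
- Normal approximation in place of the t distribution: 80.6% or 78.9% at SD 2.

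No variant tried that keeps the stated ICC comes near 91% with SD 2.

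**What SD 2 would mean for the design.**

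- With the planned sample and 232 df, the difference detectable with 90% power is 1.15 points (DE 1.834) or 1.18 points (DE 1.915).
- To keep 90% power for 1 point with 18 hospitals, the mean cluster size per joint would have to rise from 13 to about 24 (relative-efficiency form) or 30 (simpler form). That is 18 × 24 = 432 or 18 × 30 = 540 evaluable patients per joint, 576 or 720 after dropout, and 1152 or 1440 in total.

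**Side note on degrees of freedom.** With cluster-based df (2 × 9 − 2 = 16), SD 2 gives 75.5% or 73.7%, and the difference detectable with 90% power is 1.22–1.25 points. This reflects a different choice from the one the article declares and is not a consequence of the SD conflict.

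**The case against.** The strongest reply is that the working SD is disclosed. The 1.7 stands beside the ICC, the CV, the test and the degrees of freedom, and the 91%, the 117 per arm and the 312 per joint all follow from that list. On this reading the only defect is one stray introductory clause, perhaps a rounded or superseded value, and nothing shows that the true power is below 91%. Pain is also only one of several secondary outcomes. The primary outcome has its own calculation and does not use this SD: with 13 per cluster and SD 15.6 its power is about 94–95% on subject-based df. Even the unfavourable case leaves pain with about 80% power, a conventional level. Finally, the secondary analysis is a repeated-measures mixed model, so the t-test power is approximate under either SD.

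Much of this stands. The article does not show which SD is right, so 79–80% is conditional on SD 2. The primary comparison is not affected. The cluster-df figures are a separate matter.

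It does not remove the point. The article names 2 as the basis for the required numbers, and a reader cannot tell that 1.7 was meant to replace it. Rounding is an unlikely explanation, because the same paragraph gives 1.7 and the section gives its other SDs to one decimal (15.6 and 11.8). The paragraph also does more than describe a secondary outcome, since it fixes the number enrolled.

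**Conclusion.** The point holds. The paragraph contradicts itself on the SD, and its 91% power belongs to 1.7, not to the 2 it names as its basis. If 2 is the intended assumption, power for a 1-point difference is 78.6–80.3%, about 11 percentage points below the stated figure. These figures rest on the article's own cluster numbers, ICC, CV, α and subject-based df; the range reflects the two design-effect forms. The article does not settle which SD is correct. What is affected is the stated power for pain and the stated reason for enrolling 624 rather than 480, not the power for the primary outcome.

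**What to change.** State one SD for NRS pain, with its source, and make the paragraph agree with it.

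- **If 2 is right:** keep 624 and state about 80% power for a 1-point difference on the declared subject-based df, or restate the difference detectable with 90% power as about 1.15–1.18 points. If cluster-based df were adopted, the corresponding figures are about 75% and 1.22–1.25 points.
- **If 1.7 is right:** delete the reference to 2, justify 1.7, and leave 91% and 624 as they are.

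Either is a text change with no extra patients; under the first, the stated power becomes less favourable. Patients would have to be added only if the sponsor both adopts SD 2 and insists on 90% power for 1 point, which takes the total to roughly 1152–1440. That is not needed to correct the inconsistency.
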